## Abstract

**Background:**

Smoking cessation is a high-priority intervention to prevent CVD events and deaths in developing countries. While several interventions to stop smoking have been proved successful, the question of how to increase their effectiveness and practicality in developing countries remains. In this study, a newly devised evidence-based smoking cessation service package will be compared with the existing service in a randomized controlled trial within the community setting of Thailand.

**Method/Design:**

This randomized control trial will recruit 440 current smokers at CVD risk because of being diabetic and/or hypertensive. Informed, consented participants will be randomly allocated into the new service-package arm and the routine service arm. The study will take place in the non-communicable disease clinics of the Maetha District Hospital, Lampang, northern Thailand. The new smoking-cessation service-package comprises (1) regular patient motivation and coaching from the same primary care nurse over a 3-month period; (2) monthly application of piCO + smokerlyzer to sustain motivation of smoker’s quitting attempt and provide positive feedback over a 3-month period; (3) assistance by an assigned family member; (4) nicotine replacement chewing gum to relieve withdrawal symptoms. This new service will be compared with the traditional routine service comprising the 5A approach in a 1-year follow-up. Participants who consent to participate in the study but refuse to attempt quitting smoking will be allocated to the non-randomized arm, where they will be just followed up and monitored. Primary outcome of the study is smoking cessation rate at 1-year follow-up proven by breath analysis measuring carbomonoxide in parts per million in expired air. Secondary outcomes are smoking cessation rate at the 6-month follow-up, blood pressure and heart rate, CVD risk according to the Framingham general cardiovascular risk score, CVD events and deaths at the 12-month follow-up, and the cost-effectiveness of the health service packages. Intention-to-treat analysis will be followed. Factors influencing smoking cessation will be analyzed by the structure equation model.

**Discussion:**

This multicomponent intervention, accessible at primary healthcare clinics, and focusing on the individual as well as the family and social environment, is unique and expected to work effectively.

**Trial registration:**

Current Controlled Trials ISRCTN89315117

## Background

Cardiovascular diseases (CVDs) are the leading cause of morbidity and mortality globally [1]. Developing countries such as Thailand are severely affected, and the current trend is expected to get worse over the next few decades [2,3]. Reducing the CVD burden via lifestyle modification has, therefore, become an urgent public health priority [1]. There are a number of modifiable risk factors of CVDs such as smoking, physical inactivity and unhealthy diet [4], and smoking cessation is considered to have the greatest potential to prevent thousands of CVD events and deaths [4].

Thailand is a middle-income developing country with a current smoking rate of approximately 50% among males and 5-6% among females [5,6]. The smoking rate is heterogeneous across the country and could be as high as 70% among both males and females in rural areas of northern Thailand [7]. The increasing wave of CVDs in recent years is seen as the primary cause of hospitalization and rising numbers of CVD deaths within all provinces of Thailand [8]. Thailand is a country with a strict tobacco control and an effective online service for smokers attempting to give up smoking [9,10]. However, previous surveys of tobacco use in Thailand have revealed unique features of its smokers, such as the high smoking rate in rural areas and high prevalence of “roll-your-own” cigarettes and household smoking [10]. A smoking cessation service reaching to the primary health care is key to prevention of CVD in Thailand. Enhancing the implementation of community-based smoking cessation programs would avert the health and economic burden of CVDs [10,11].

A randomized controlled trial, seeking an effective smoking cessation service in the primary care setting of developing countries, is very rare and has yet to be conducted in Thailand [12]. While smoking cessation interventions, such as brief counseling, nicotine replacement and therapy, etc., were reported to be effective, the question of how to increase their effectiveness and practicality remains [11,13]. To function as part of primary health care, a culturally-tailored smoking cessation service, which is feasible within the individual, social and financial capitals of the target setting, is a necessity. In this study, a newly devised evidence-based smoking cessation service package will be compared, in a randomized controlled trial, with the existing service within the community setting of northern Thailand.

## Methods/Design

### Study hypothesis

A smoking cessation service package comprising continuous motivation by a single designated nurse, application of a smokerlyzer, continuous family support and nicotine replacement therapy, based on individual need, will lead to a more successful behavioral change in patients at risk from cardiovascular diseases, as compared to the conventional smoking-cessation service [14].

### Study objectives

The primary objective is to compare the smoking cessation rate between a new evidence-based smoking cessation service package and the conventional 5 A approach to smoking cessation at the 1-year follow-up.

 The secondary objectives are:

1. to compare the smoking cessation rate at the 6-month follow-up.

2. to compare the CVD risk by Framingham general cardiovascular risk score among intervention and control groups at the 1-year follow-up.

3. to determine the characteristics of those who have successfully given up smoking and the determinants of behavioral change.

4. to determine the characteristics of relapse smokers after 6 months of cessation and the determinants of behavioral change.

5. to compare the cardiovascular disease events between ex-smokers, reduced smokers and continuous smokers at the 1-year follow-up.

6. to determine the cost-effectiveness of the new smoking cessation service package.

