### Inclusion criteria

1. Current smokers with diabetes.

2. Current smokers with hypertension.

3. Current smokers with both diabetes and hypertension.

4. Smokers who have never succeeded in giving up smoking.

5. Male or female.

6. Aged 35–80 years.

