### Definitions

#### Smoking cessation

Smoking cessation is defined as the stopping of smoking for a period of at least 6 months and confirmed by the assessment of carbon monoxide (CO) in the smoker’s expired air using a smokerlyzer.

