### Outcome measurements

#### Smoking cessation

This would be assessed by self-reported quitting confirmed by breath analysis of the level of carbon monoxide (CO) in expired air. A piCO ^+^ Smokerlyzer® [21] carbon monoxide monitor will be used for this assessment on the first visit, and again on the 6- and 12-month visits. It is a clinically proven way to determine the carbon monoxide level and easy to use in primary care. In previous studies, the Smokelyzer has been shown to have positive, predictive values for detecting smoking, at more than 95% [12,22]. It can also serve as a motivational tool for giving up smoking. Nicotine dependence will be assessed by the Fagerstrom Nicotine Dependence Test and the Nicodep Test [18,20]. The self-reported smoking cessation rate is ascertained by asking participants the number of cigarettes smoked in the preceding 24 h.

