#### CVD events and death

Participants will be followed up by nurse-administered, structured questionnaires at the 6- and 12-month visits, ascertaining medical history, lifestyle and health-related behaviors. During each questionnaire, participants will be asked whether they have had a CVD event referred to the community hospital; any reported CVD event will be confirmed by reviewing the NCD network medical records [25].

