### Sample size

A total of 328 participants will be randomized to have 164 in the new service arm and 164 in the routine service arm. The sample size for the randomized controlled trial was calculated to have a power of 80% and 95% confidence interval so as to show the difference in primary and secondary outcomes, and the CVD incidence between the new package arm and the routine service arm. It was calculated using the power sample size calculation of Stata version 11, based on the previous year’s smoking cessation rate at the MH (9%), and the estimated cessation rate of the evidence-based package (24%). Additionally, the calculated sample size was increased by 20% to compensate for loss to follow-up.

The sample size for the additional non-randomized arm was calculated at a ratio of 1:3 compared to the total size of the two intervention arms. The power of 90% and 95 percent confidence interval will suffice to see the difference in CVD events between ex-smokers and continuous smokers, assumed as 0.1 and 0.25. Totally the sample size is 440 participants.

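### Secondary objective 5 compares one-year CVD events between groups defined by smoking status reached during that same year, with no rule for when status is fixed or how deaths are classed

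*Protocol article*

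**What the plan says.** All places are in the protocol article.

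- **Study objectives**, secondary objective 5: "to compare the cardiovascular disease events between ex-smokers, reduced smokers and continuous smokers at the 1-year follow-up".
- **Sample size**: "The power of 90% and 95 percent confidence interval will suffice to see the difference in CVD events between ex-smokers and continuous smokers", with assumed event proportions of 0.10 and 0.25. The total is 440, of whom 328 are randomized.
- **Inclusion criteria**: all disease criteria require current smoking, for example "Current smokers with both diabetes and hypertension". Nobody is an ex-smoker at time zero.
- **Definitions**, smoking cessation: "Smoking cessation is defined as the stopping of smoking for a period of at least 6 months", with CO confirmation.
- **Outcome measurements**, smoking cessation: the CO monitor "will be used for this assessment on the first visit, and again on the 6- and 12-month visits". Table 2 adds self-report at month 3.
- **CVD events and death**: "Participants will be followed up by nurse-administered, structured questionnaires at the 6- and 12-month visits". Events are therefore collected over the same 12 months.
- **CVD risk, CVD events and CVD death** (analysis plan): CVD events and deaths are compared by randomized arm, then across the three arms with a Cox model. The comparison by quitting status in that section covers Framingham score, blood pressure, heart rate and BMI. No method is given there for CVD events by smoking status.

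**The concern.** The comparison needs a group that cannot exist at enrolment. A participant becomes an ex-smoker only after at least 6 months of abstinence and a confirming CO test, while events are counted from day one. Two errors can follow.

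1. **Reverse causation.** A smoker has a non-fatal event in the first half-year, quits because of it, and by month 12 satisfies the cessation definition. The event occurred while smoking but is counted against quitting.
2. **Immortal time.** Whoever dies before the confirming visit cannot be confirmed as an ex-smoker. If such deaths are put with the smokers, fatal events are moved out of the ex-smoker group.

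Both arise from the order of event and quitting, so adjustment for the confounders in Table 3 removes neither. At stake is a listed secondary objective with its own power statement: the result could suggest benefit or harm from quitting when there is none.

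**Working it through.** **1. The plan's own figure.** For 0.25 vs 0.10, 90% power, two-sided 5% (two-sided is assumed), smaller group to larger 1:3, pooled-variance formula:

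- Mean proportion = (0.25 + 3 × 0.10)/4 = 0.1375.
- n = [1.96 √(0.1375 × 0.8625 × 4/3) + 1.2816 √(0.1875 + 0.09/3)]² / 0.15² = 84.3.
- With continuity correction, n = 93. Then 93 × 1.2 = 112, and 328 + 112 = 440.

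The stated total is thus consistent with this contrast. Reproduced this way, however, all 328 randomized participants stand in for the ex-smokers.

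**2. Expected ex-smokers.** From the cessation rates in Sample size: 164 × 0.24 + 164 × 0.09 = 54, assuming none in the refusing arm. That leaves 440 − 54 = 386 others.

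**3. Size of the bias when quitting has no effect (true ratio 1).** Let R be annual risk, q the share of spontaneous quitters, f the fatal share of events, p the share of early-event survivors who quit because of the event, and e = 1 − √(1 − R) the 6-month risk under constant hazard. I take q = 16.5%, the mean of 9% and 24%. R = 10% and 25% are the protocol's figures; R = 3% is illustrative. The documents give neither f nor p.

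*Status at month 12, deaths unclassified, some quitting prompted by events (shown for f = 0):*

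- Ex-smoker risk = [qR + (1−q)ep] / [q + (1−q)ep].
- Smoker risk = (R − ep)/(1 − ep).
- R = 25%, p = 20%: e = 0.134; 0.340/0.229 = 1.48.

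| R | p = 20% | p = 40% |
|---|---|---|
| 25% | 1.48 | 1.98 |
| 10% | 1.59 | 2.28 |
| 3% | 1.65 | 2.44 |

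Removing 10-30% of events as unclassified deaths moves these little (highest value 2.47). With q = 54/440 = 12.3% they are larger, for example 2.20 instead of 1.98.

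*Deaths classed as smokers, no prompted quitting:*

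- Ex-smoker risk = R(1−f)/(1−Rf).
- Smoker risk = R[(1−q)+qf] / [(1−q)+qRf].
- R = 25%, f = 10%: 0.2308/0.2537 = 0.91.

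| R | f = 10% | f = 30% |
|---|---|---|
| 25% | 0.91 | 0.73 |
| 10% | 0.89 | 0.69 |
| 3% | 0.89 | 0.67 |

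*Deaths unclassified and no prompted quitting:* the ratio is 1.00.

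*Both errors together* (simulation, f and p each 20% or 40%): about 0.9 to 1.8.

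**4. Landmark check.** In the simulation, fixing status at month 6 in event-free participants and counting only later events returned the null ratio to 0.98-1.02.

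**5. Power, 0.10 vs 0.25 (pooled-variance test).**

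- *Full year, 54 vs 386, no dropout.* Pooled proportion 0.2316; standard error 0.0612 under the null and 0.0464 under the alternative; Φ[(0.15 − 1.96 × 0.0612)/0.0464] = 74%. After dropout: 62-64%.
- *Month-6 landmark.* Six-month risks 1 − √0.90 = 0.051 and 1 − √0.75 = 0.134; event-free at month 6: 54.12 × 0.949 = 51 and 385.88 × 0.866 = 334. Standard errors 0.0492 and 0.0360; Φ[(0.0827 − 1.96 × 0.0492)/0.0360] = 35%. After dropout: 27-28%. This assumes that the 54 eventual quitters are those abstinent at month 6.

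**The case against.** The strongest reply is that the article does not fix the analysis being criticised. In objective 5 the one-year phrase may date the outcome, as it does in objectives 1 and 2, and not the classification. Status is also measured at months 3 and 6. The stated CVD event analyses are by arm, and a landmark or time-varying exposure could appear in an analysis plan that is not shown. This stands as a limit on the claim: month-12 classification is the natural reading, not a written rule. It does not remove the point, because the objective as worded defines its groups by status reached after enrolment. Had month-6 status been used for all 12 months of events, the first 6 months would still precede or overlap classification.

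Three stronger inferences are tempting and unsupported.

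- *CVD deaths among ex-smokers are zero by construction.* No coding rule for deaths is given. A continuing smoker must also be alive to be classified at month 12, and if deaths are left out of every group this mechanism disappears (ratio 1.00 above).
- *The comparison must flatter quitting, or must penalise it.* The two errors act in opposite directions.
- *The trial's CVD analyses as a whole are compromised.* Arm membership is set at enrolment, so the arm comparisons carry no immortal time from this source.

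It is also fair that sampling error may exceed the bias. At 3% annual risk, 54 ex-smokers yield about 54 × 0.03 = 1.6 events.

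**Conclusion.** The concern holds for secondary objective 5 and its power statement only. The groups form during the period in which events are counted, and the article neither dates the classification nor states how deaths are classed. With status taken at one year and no true effect, event-prompted quitting gives a ratio of about 1.5-2.5 with deaths unclassified, and classing deaths as smokers gives about 0.67-0.91. The fatal share, the prompted-quit share and constant hazard are assumptions, so the figures show possible size and not an expected result; the net direction cannot be known in advance. The primary outcome and the arm-based CVD analyses are unaffected. Separately, the 90% power claim is not met with the expected 54 quitters: about 74% before dropout, even if the bias is ignored.

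**What to change.** State for objective 5 when smoking status is classified and how deaths and missed visits are handled, and adopt one of two analyses:

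- a Cox model with smoking status as a time-varying covariate, updated at the scheduled visits; or
- a month-6 landmark in participants alive and event-free at that visit, classified by CO-confirmed abstinence at month 6, counting only later events. The definition requiring "the stopping of smoking for a period of at least 6 months" should not be used at the landmark, because at month 6 only those who stopped essentially at enrolment could meet it.

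Label the result observational. Withdraw the 90% power statement for this contrast, or restate it for the group sizes expected.

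**Cost.** No new data are needed. The landmark discards events in the first 6 months, counts later quitters as smokers, and leaves about 35% power on the protocol's own rates. The time-varying model gains little over it, because CO is scheduled only at baseline, month 6 and month 12; an earlier update would rest on month-3 self-report.

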### Study design

The study design is essentially that of a randomized controlled trial (RCT) comparing two parallel groups. However, given the nature of smoking cessation research, an additional, third arm will be included for smokers who refuse to try to give up smoking and so are unable to be randomized into either of the treatment service arms. Consequently, it will be a randomized, controlled trial with an additional non-randomized arm. The study flow chart is as follows.

### Study site

Thailand is the study site. Maetha Hospital (MH) is the leading center in this trial. The study will be implemented via the MH network of mobile NCD clinics at seven primary care units (PCU) within the Maetha district. Study site PCUs were chosen based on the eligibility criteria of (1) the presence a regular mobile NCD clinic; (2) a smoking rate among NCD clinic attendants not less than 10%; (3) willingness of the PCU to join the study.

### Study population

The study population will comprise smokers with a high CVD risk, having either hypertension or diabetes, or both.

### Eligibility criteria for individual patients to enroll in the study

The selection of participants will be based on the following inclusion and exclusion criteria:

### Inclusion criteria

1. Current smokers with diabetes.

2. Current smokers with hypertension.

3. Current smokers with both diabetes and hypertension.

4. Smokers who have never succeeded in giving up smoking.

5. Male or female.

6. Aged 35–80 years.

### Exclusion criteria

1. Any female patients who are pregnant or planning to become pregnant.

2. Patients aged younger than 35 years.

3. Patients with documented type I diabetes.

4. Patients with cancer.

5. Patients with severe chronic pulmonary diseases using home oxygen therapy.

6. Patients with a known diagnosis of a previous cardiovascular disease (CVD) event.

### Ethical approval

Ethical approval of the study protocol was granted by the Juntendo University Ethics Committee, Japan, by permission no. 2012194, and the Institutional Review Board at Boromarajonani College of Nursing, Lampang, Thailand, by approval number E2556/005. The study has been registered as an international current control trial at the ISRCTN registry. The ISRCTN registration no. ISRCTN89315117 was assigned on 9 July 2013 [14] Acronym of the study is ESCAPE: *Effective Smoking Cessation Augmented PackagE*.

Written informed consent will be requested from eligible individuals. Participants can freely decide to participate in the trial after being informed about the study (Autonomy). There are no racial or ethnical criteria for inclusion in the study (Equity). Participants in each arm of the study will receive routine health services, and those in the new-service intervention arm will receive some trial-related service benefits, such as breath analysis by smokerlyzer and provision of nicotine replacement therapy if suffering from nicotine withdrawal. There will be no or minimal introduction of risk to the participants but instead an expected CVD risk reduction via the smoking cessation intervention and study-related health education (Beneficence).

### Enrollment and randomization

To ensure the required sample size, smoking prevalence among diabetes and hypertension clinics attendants was surveyed. The study site is within the community setting and coupling with non-communicable disease (NCD) clinics, which is expected to promote the smoker’s access to enrollment in the study. Those meeting eligibility criteria will be invited to participate in the study in their routine visit to the PCU. The participants who consent and decide to attempt to stop smoking will be randomly allocated into either the routine service intervention arm or the new service intervention arm. Those who refuse to attempt quitting smoking will be recruited to the non-randomized arm (Figure 1). The randomization site is the NCD clinic at the PCU. Randomization is blocked with the center as a stratum. Random sequences are generated by the statistician on the basis of blocks of 24. The allocated arm for each participant will be provided to the study sites PCUs in opaque, sealed envelopes.

**Figure 1 F1:**
[figure not shown]
**Flow chart for enrollment and follow-up plan for RCT with an additional non-randomized arm.** Note: *Fagerstrom nicotine dependence test, *NRT* nicotine replacement therapy. *Bold arrows* show the randomized trial, and the *dotted arrow* shows the non-randomized arm.

### Concealment of allocation

Requesting of consent and randomization will precede explanations to patients about the procedures within their allocated study arm. The allocated arm will be revealed to the patient when the research nurse opens the sealed envelope following recruitment, consent and the participant’s agreement to attempt to give up smoking. Participants will know the details only of the study arm to which he/she has been randomly allocated. The investigators cannot anticipate into which intervention arm a participant will be allocated.

### Blinding

Double blinding is not possible because of the nature of trials for health care service intervention. The PCU nurse will know the intervention arms. However, possible investigator’s bias will be minimized, and anticipation of the allocated arm will be prevented by the block randomization procedure [15].

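### Blocking is wrongly credited with preventing anticipation of the arm; concealment rests on the sealed envelopes, and a single block size of 24 leaves a small, avoidable predictability

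*Protocol article*

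**What the plan says.** The randomization method is in the protocol article under Enrollment and randomization. It says "Randomization is blocked with the center as a stratum" and "Random sequences are generated by the statistician on the basis of blocks of 24". No other block size is mentioned. It also says "The randomization site is the NCD clinic at the PCU" and "The allocated arm for each participant will be provided to the study sites PCUs in opaque, sealed envelopes". Study site gives the number of units as "seven primary care units (PCU) within the Maetha district".

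Concealment of allocation says that a research nurse opens the envelope after recruitment, consent and the participant's agreement to try to stop. It concludes: "The investigators cannot anticipate into which intervention arm a participant will be allocated".

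Blinding concedes that double blinding is impossible and that "The PCU nurse will know the intervention arms". It then says that investigator bias will be minimized and that "anticipation of the allocated arm will be prevented by the block randomization procedure". The envelopes are not mentioned there.

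**The concern.** The Blinding section names the wrong mechanism. Permuted blocks force the arms to equal numbers at the end of each block. That constraint is what lets an observer infer the remaining allocations from those already made. Simple randomization carries no such information. Blocking also does nothing about bias after the arm is known, so it cannot be the reason that investigator bias is minimized.

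The design has the usual ingredients for inference from past allocations: one stated block size, a separate sequence per center, envelopes opened on site, and open treatment.

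This trial also has an unusual branch just before the envelope is opened. A participant who agrees to try to quit is randomized, and one who refuses goes to the non-randomized arm. Someone who could foresee the next arm could influence that decision or its timing. The randomized groups would then differ in who was admitted to them, which is selection bias in the primary comparison of cessation at one year.

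**Working it through.** **Inputs from the article.** Block size 24 and center as stratum (Enrollment and randomization); seven units (Study site); 328 randomized, 164 per arm, so 1:1 (Sample size).

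**Assumptions.** Each primary care unit is a center. Recruitment is even, so 328/7 = 46.9, taken as 47 per unit. The observer knows the block size and every earlier allocation at the unit, and always guesses the arm with more places left. The article gives no predictability figure of its own to reproduce.

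**Certain allocations in one full block.** With m = 12 per arm, the expected number of allocations that are fully determined is 2m/(m + 1) = 24/13 = 1.85, or 1.85/24 = 7.7%. The 24th is always determined, and none before the 13th can be.

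**Correct guesses in one full block.** Half are right by chance, plus an excess of (2^24/C(24,12) − 1)/2 = (16,777,216/2,704,156 − 1)/2 = (6.204 − 1)/2 = 2.60. The total is 12 + 2.60 = 14.60 of 24, or 60.8%, against 50% under simple randomization.

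**A unit with 47 allocations.** This is one full block plus 23 places of a second. The missing 24th place would have been certain and guessed correctly, so one is subtracted from the second block.
- Certain: 1.846 + 0.846 = 2.69 of 47 = 5.7%. Over seven units: 7 × 2.69 = 18.8, about 19.
- Correct guesses: 14.60 + 13.60 = 28.20 of 47 = 60.0%.

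**Effect of varying the block size.** Units of 47 allocations were simulated with a guesser who knows the set of sizes but not their order, and who updates on every allocation.

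| Block sizes | Certain | Guessed correctly | Mean imbalance in a unit |
|---|---|---|---|
| Fixed 24 | 5.8% (exact value 5.7%) | 60.0% | 1.0 |
| 20, 24, 28 | 0.8% | 59.7% | 1.5 |
| 16 to 32 | 0.3% | 59.6% | 1.7 |

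A repeat simulation agreed with these figures to within 0.1 percentage point. For 328 participants, 0.8% is about 3 certain allocations (0.008 × 328 = 2.6) instead of about 19.

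**Why not smaller blocks.** A fixed block of 4 would give 33% certain and 70.8% guessed correctly, which is worse on both counts. The gain comes from varying the size around 24, not from shrinking it.

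**The case against.** The strongest reply is that the property claimed is largely delivered, only by a mechanism that the Blinding section does not name. The statistician generates the sequence, the envelopes are opaque and sealed, and they are opened only once the participant is committed. Twenty-four is also a large block. This stands: a reader might infer that the trial has no protection against anticipation, and the article does not support that. The envelopes hide the next allocation. They do not stop inference from earlier ones, so a small gap remains.

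The second reply is that the observer in the calculation is hypothetical. This also stands. A reader might infer that an unblinded unit nurse opens the envelopes, counts the arms and decides who is asked to quit. The article says only that the unit nurse knows the arms. It names a research nurse as the one who opens the envelope, without saying whether this is the same person. It describes no tally, does not say whether site staff know the block size, and puts the question about quitting in the passive. Even the word "fixed" is a reading, though a fair one, of a single stated size.

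The third reply concerns size. Counting 14 completed blocks (two per unit) gives 14 × 24/13 = 25.8, about 26 certain allocations. But 14 blocks hold 336 participants and the trial randomizes 328, so about 19 is the right figure, and it is an upper bound for this pattern of recruitment. Varied blocks also barely change overall guessability. What they remove is nearly all of the certainty.

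None of these replies makes the sentence in Blinding correct.

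**Conclusion.** The point holds as a wrongly attributed property with a small residual weakness. Blocking does not prevent anticipation or minimize investigator bias, and the absolute statement under Concealment of allocation goes too far for an open-label trial with one stated block size per center.

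The exposure is at most about 19 of 328 allocations known with certainty (5.7% exactly, 5.8% by simulation), with about 60% guessed correctly. This rests on units serving as centers, even recruitment of about 47 per unit, and an observer with the block size and a complete record. The article establishes none of these three. No bias in the primary result has been shown or quantified, and none should be inferred. The case for acting is that the statement is wrong and the remedy is cheap.

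**What to change.** 1. Reword Concealment of allocation and Blinding. Say that concealment rests on the opaque sealed envelopes opened after consent and agreement to try to quit, and that blocking serves only to balance numbers. Remove the claims that blocking prevents anticipation or minimizes investigator bias, and soften the absolute statement about investigators.
2. For envelopes not yet issued, have the statistician generate each unit's sequence with randomly varied block sizes around the present one, for example 20, 24 and 28, and withhold the sizes from unit staff. State in the protocol that the sizes are varied and withheld, without listing them.

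The cost is a short wording amendment, a new list and envelope set for the remaining allocations, and about half a participant more mean imbalance within a unit (1.5 instead of 1.0). The trial status is recruiting, so the second change can reach only the envelopes still to be issued. The first can be made at any time.
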